### Ethics

The study will be performed in accordance with the declaration of Helsinki and the Dutch "Wet Medisch-wetenschappelijk Onderzoek met Mensen" (Medical Research Involving Human Subjects Act). The IRB of the University Medical Center Utrecht approved the protocol on the 4^th ^of March 2008. Secondary approval was sought from all local ethics committees. Informed consent will be obtained from each participating patient in oral and written form prior to randomisation. The PYTHON trial is registered in the ISRCTN register with identification number ISRCTN18170985. After approval of the protocol, 2 amendments were approved by the ethics board. These amendments followed new regulations in the Netherlands for the reporting of (serious) adverse events. The content of both amendments is incorporated in this protocol.

## Statistical Aspects

### Sample size calculation

The PYTHON trial is a superiority trial, hypothesizing a reduction in the primary endpoint in favour of early EN as compared to the current practice of an oral diet and EN, if necessary at 72 hours after admission. Data from patients in the PROPATRIA trial are used to calculate sample size [23]. All patients in the placebo-arm of the PROPATRIA trial received EN via a nasojejunal feeding tube. Patients from the PROPATRIA trial that fulfilled the PYTHON inclusion criteria (predicted severe acute pancreatitis < 24 hours after admission) were evaluated. In these patients EN was initiated after a median of 3 days. This equals the standard group in the PYTHON trial. In 39% of these patients an infection (bacteraemia, pneumonia, infected necrosis) occurred. The mortality in the placebo arm of PROPATRIA was 6%. All studies included in a meta-analysis performed by our group on EN versus PN that initiated EN within 24 hours after admission were selected [17]. In these patients (receiving EN within 24 hours), infections were diagnosed in 22% and mortality was 5%. Therefore, the expected reduction in mortality is only 1%. When mortality and infections are combined in the primary composite endpoint, an absolute reduction of 18% is expected (from 40 to 22%). With 80% power, two-sided 5% alpha and 1% loss to follow-up the sample size was set at 208 patients [http://www.stat.ubc.ca/~rollin/stats/ssize/b2.html].

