### Primary endpoint

The primary endpoint is a composite of mortality or infections (i.e. bacteraemia, pneumonia and infected necrosis; see Table 1 for definitions) occurring during hospital admission or within 6 months following randomisation. Re-admission within 10 days after initial hospital discharge is considered part of the index admission.

**Table 1 T1:** Primary endpoint: definition of infections

Infection	Definition
Infected pancreatic necrosis	Positive culture of pancreatic or peripancreatic necrotic tissue obtained by means of fine-needle aspiration or from the first drainage procedure or operation, or the presence of gas in the fluid collection on contrast-enhanced CT.

Bacteraemia	Positive blood culture. For non-pathogens (eg. coagulase negative staphylococci) at least 2 samples have to be positive.

Pneumonia	Coughing or dyspnoea, radiography with infiltrative abnormalities, raised inflammatory variables and positive sputum culture. On the intensive care unit a positive endotracheal culture is mandatory.

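### The 22% used as the early-arm rate of death or infection is the infection rate alone, so the stated 80% power holds only if essentially every early-arm death also had an infection

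*Protocol article*

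**What the plan says.** The Primary endpoint section counts a patient as an event for death or for infection: "The primary endpoint is a composite of mortality or infections (i.e. bacteraemia, pneumonia and infected necrosis; see Table 1 for definitions".

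The Sample size calculation section then gives the planning inputs (all percentages):

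- Control infections, from those patients of an earlier trial who met the PYTHON inclusion criteria: "In 39% of these patients an infection (bacteraemia, pneumonia, infected necrosis) occurred".
- Control mortality: "The mortality in the placebo arm of PROPATRIA was 6".
- Early-arm infections and mortality, from studies in a meta-analysis that started enteral nutrition within 24 hours: "In these patients (receiving EN within 24 hours), infections were diagnosed in 22% and mortality was 5".
- Composite: "When mortality and infections are combined in the primary composite endpoint, an absolute reduction of 18% is expected (from 40 to 22".
- Size: "With 80% power, two-sided 5% alpha and 1% loss to follow-up the sample size was set at 208 patients".

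**The concern.** A composite of death or infection cannot be smaller than its infection component, and it is larger by exactly the share of patients who die without an infection. On the printed figures that share is 40 − 39 = 1 point in the control arm and 22 − 22 = 0 points in the early arm. The article gives no reason for the difference.

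The effect is to widen the planned difference from 17 points (39 − 22) to 18. With 22% infections and 5% mortality, the early-arm composite can lie anywhere from 22% (every death had an infection) to 27% (none did). The plan uses the most favourable end of that range.

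What is at stake is how a null result is read. The Discussion presents the trial as filling the gap left by the lack of an adequately powered trial of timing, and 208 is sized to 80% with no reserve. If some early-arm patients die without an infection, the chance of missing the planned effect is larger than the stated 20%.

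**Working it through.** **Inputs.** Control: infection 39%, mortality 6%, composite 40%. Early arm: infection 22%, mortality 5%, composite 22%. Two-sided 5% alpha, 80% power, 1% loss, 208 patients (all from Sample size calculation). Allocation 1:1 (Study Population).

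**Formulas.** Pooled-variance normal approximation for two proportions, no continuity correction, with p̄ = (p₁ + p₂)/2:

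- n per arm = [1.960·√(2p̄(1−p̄)) + 0.842·√(p₁(1−p₁) + p₂(1−p₂))]² / (p₁−p₂)²
- power = Φ{ [ |p₁−p₂|·√n − 1.960·√(2p̄(1−p̄)) ] / √(p₁(1−p₁) + p₂(1−p₂)) }

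**Step 1: reproduce the plan's figure.** For 40% vs 22%, p̄ = 0.31, the pooled term is √(2·0.31·0.69) = 0.6541 and the unpooled term is √(0.24 + 0.1716) = 0.6416. This gives n = 102.45, so 103 per arm and 206 in total. With 1% loss, 206/0.99 = 208.1, which matches the stated 208. Power at 103 per arm is Φ[(1.8268 − 1.2819)/0.6416] = Φ(0.849) = 80.2%. The stated size and power therefore follow from 40% vs 22%, and 22% is the value that was used.

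**Step 2: treat the arms alike on the printed figures.** There are three ways to do so:

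- Add 1 point to both arms: 40% vs 23%. Power at 103 per arm is Φ[(1.7253 − 1.2875)/0.6458] = Φ(0.678) = 75.1%.
- Apply the control share of deaths without infection (1/6) to early-arm mortality: 22 + 5/6 = 22.8%, so 40% vs 22.8%.
- Add deaths to neither arm: 39% vs 22%.

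**Step 3: the range over the unknown overlap.** Hold control at 40% and let the early-arm composite run from 22% to 27%. The columns use 103 per arm (208 less 1% loss) and 104 per arm (no loss).

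| Control vs early | Reading | Power, 103 per arm | Power, 104 per arm |
|---|---|---|---|
| 40 vs 22% | as planned; every early-arm death had an infection | 80.2% | 80.6% |
| 40 vs 22.8% | same 1/6 share in both arms | 76.0% | 76.4% |
| 39 vs 22% | infections only in both arms | 75.9% | 76.3% |
| 40 vs 23% | 1 point added in both arms | 75.1% | 75.5% |
| 40 vs 24% | 2 points of early-arm deaths without infection | 69.5% | 69.9% |
| 40 vs 25% | 3 points | 63.4% | 63.8% |
| 40 vs 27% | bound: no early-arm death had an infection | 50.7% | 51.1% |

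**Step 4: check on the approximation.** Exact enumeration of the same uncorrected test gives 80.6-81.1% at 40% vs 22% and 75.4-76.0% at 40% vs 23%. The drop of about 5 points does not come from the normal approximation.

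**For scale only.** Under the same formula, 80% power would need 117 per arm for 40% vs 23% (234 in total; 234/0.99 = 236.4) and 114 per arm for 39% vs 22% (228 in total; 228/0.99 = 230.3).

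**The case against.** **Nothing is miscalculated.** This stands for the step from rates to sample size: 208 and 80% reproduce. Each composite is also possible on its own, since 22% lies within 22-27% and 40% lies within 39-45%. The criticism concerns an input and the condition it carries.

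**Rounding could explain the pattern.** This stands in part. Suppose, as an assumption, infection rates of 39.4% and 21.6% with 0.8 points added in both arms. The composites are 40.2% and 22.4%, which print as 40 and 22 under one rule, and power is 79.1-79.5%. With 39.4% and 21.8% and 0.4 points added, the composites are 39.8% and 22.2% and power is 78.4-78.8%. These are illustrations, not limits. If the same amount is added in both arms, the printed figures need a control composite of at least 39.5 and an early one below 22.5, so the difference exceeds 17. They also need control infections below 39.5 and early infections of at least 21.5, so the difference is below 18. Rounding can therefore recover much of the lost power or almost none of it, and the article does not say which.

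**The overlap need not be the same in both arms.** This also stands. The two arms come from different sources, the 40% may be a direct count in the eligible subset, and the early-arm overlap of deaths and infections is not reported. Carrying the control pattern to the early arm is a convention, not a fact from the document.

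For these reasons a reader might infer more than the article supports:

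- That the true power is 75-76%. That figure belongs to like-for-like handling of the printed whole percentages.
- That the two arms were demonstrably combined by different rules. The printed figures suggest it, but rounding could produce the same print.
- That power may be as low as 51%. That is a logical bound requiring that no early-arm death had an infection; it is not an estimate.
- That the mixed denominators (39% from the eligible subset, 6% from the whole placebo arm) distort the power. If 40% was counted directly, the 6% did not enter it, and no power figure changes.

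**Conclusion.** The point holds in a limited form. The early-arm composite equals the infection rate alone, so the stated 80% is conditional on essentially no early-arm patient dying without an infection. The article neither states that condition nor gives data for it, and its control arm does not show the same pattern on the printed figures.

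On the printed rates, all three like-for-like treatments agree on about 75-76% power, a loss of 4-5 points. That result assumes the printed percentages are taken at face value and the arms are handled alike. With rounding of the source rates, 78-79% is also compatible.

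Severity is moderate. The endpoint, significance level and intention-to-treat comparison are unaffected, and the risk ratio with its 95% confidence interval (Analyses section) will show the precision achieved whatever the planned power was.

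**What to change.** In the Sample size calculation section, derive both composite rates by the same rule. The best way is to count patients with death or infection directly in the source patients of each arm, and to say that this was done. Then restate the power of 208 patients at the resulting rates; on the rates now printed that is about 75-76%.

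If 40% versus 22% is kept, state that 80% power is conditional on no early-arm death without an infection. Show power over a range of early-arm rates, for example 22% (80%), 23% (75%), 24% (69-70%) and 25% (63-64%), with 27% (51%) as the bound.

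The cost is a few sentences in one section. No extra patients and no change to trial conduct are needed. The only downside is a slightly less favourable stated power.

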### Descriptive statistics

For dichotomous data, frequencies will be presented. Continuous data will be presented as mean and standard deviation or median and interquartile range. Baseline characteristics (all prior to randomisation) are: age, sex, body mass index, etiology of pancreatitis, American Society of Anesthesiologists (ASA) classification, co-morbidity (i.e. cardiovascular disease, pulmonary disease, chronic renal insufficiency or diabetes), predicted severity (APACHE-II, Imrie score, CRP, BUN), presence of organ failure or multi-system organfailure, Marshall score, amount of intravenous fluids administered prior to randomisation, time from onset of symptoms to randomisation, time from onset of symptoms to admission and number of referrals prior to randomisation.

### Analyses

All analyses will be according to the intention-to-treat approach in which all randomised patients are included, regardless of adherence to study protocol. After the last patient in the trial has completed follow-up, an adjudication committee blinded for treatment allocation will evaluate each patient using the raw data for the possible occurrence of the primary endpoint. Disagreements will be resolved in a plenary consensus meeting. Occurrences of the primary and secondary endpoints are compared between the treatment groups. Results are presented as risk ratios with corresponding 95% confidence intervals. A two-tailed P < 0.05 is considered statistically significant.

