**Methods/Design:**

The PYTHON trial is a randomised controlled, parallel-group, superiority multicenter trial. Patients with predicted severe acute pancreatitis (Imrie-score ≥ 3 or APACHE-II score ≥ 8 or CRP > 150 mg/L) will be randomised to EN within 24 hours or an oral diet and EN if necessary, after 72 hours after hospital admission.

During a 3-year period, 208 patients will be enrolled from 20 hospitals of the Dutch Pancreatitis Study Group. The primary endpoint is a composite of mortality or infections (bacteraemia, infected pancreatic or peripancreatic necrosis, pneumonia) during hospital stay or within 6 months following randomisation. Secondary endpoints include other major morbidity (e.g. new onset organ failure, need for intervention), intolerance of enteral feeding and total costs from a societal perspective.

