### Study Population

All patients admitted with a first episode of acute pancreatitis to one of the 20 participating hospitals of the Dutch Pancreatitis Study Group (DPSG, hospitals are listed below) will be assessed for eligibility within 24 hours after hospital admission. Potential eligible patients are followed during the first 24 hours after admission until eligibility is established or the first 24 hours following admission have passed. If patients are classified as 'predicted severe' acute pancreatitis, they are included and stratified for hospital and APACHE-II score <13 or ≥13 and randomised in a 1:1 ratio, to receive early EN or an oral diet or EN if necessary at 72 hours after admission (figure 1) [20].

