### Randomisation

Randomisation is performed centrally by the study coordinator using an internet randomisation module (Julius Center for primary care and health sciences, University Medical Center Utrecht, the Netherlands). Randomisation is stratified according to the predicted severity of disease ('predicted moderate severe' vs. 'predicted very severe'; APACHE-II < 13 or ≥ 13) and according to hospital. Permuted-block randomisation with varying block size is used and block size is concealed to all local investigators.

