### Additional analyses

To evaluate potential differences in systemic inflammatory response after randomisation, the area under the curve of APACHE-II and Marshall scores from randomization to day 7 will be calculated and compared between treatment groups. A predefined subgroup analysis will be done for the occurrence of the primary endpoint in patients with an APACHE-II < 13 or an APACHE-II ≥ 13. The precise relation between the primary endpoint and the time between start of symptoms and start of EN will be analyzed using a generalized linear model with logarithmic link function and Bernouilli distribution, with independent variables time (between start of symptoms and start of EN), time*time, APACHE-II score prior to randomization, hospital and co-morbidity (i.e. cardiovascular disease, pulmonary disease, chronic renal insufficiency or diabetes) [24].

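### Randomisation is stratified by APACHE-II and hospital, but the primary comparison reads as an unadjusted risk ratio, which gives up a little precision if APACHE-II is prognostic

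*Protocol article*

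**What the plan says.** All places are in the protocol article.

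- **Randomisation:** "Randomisation is stratified according to the predicted severity of disease" (APACHE-II <13 or ≥13) "and according to hospital. Permuted-block randomisation with varying block size is used". Study Population adds that patients are "randomised in a 1:1 ratio".
- **Abstract, Methods/Design:** "208 patients will be enrolled from 20 hospitals of the Dutch Pancreatitis Study Group".
- **Analyses:** "Occurrences of the primary and secondary endpoints are compared between the treatment groups. Results are presented as risk ratios with corresponding 95% confidence intervals", with a two-sided 5% significance level. No test, model, stratum or covariate is named for this comparison.
- **Additional analyses, subgroup:** "A predefined subgroup analysis will be done for the occurrence of the primary endpoint", split at APACHE-II 13.
- **Additional analyses, timing model:** a log-link model of the primary endpoint on the time from symptoms to EN lists APACHE-II, hospital and co-morbidity as covariates. Treatment arm is not among its terms.
- **Additional analyses, scores:** "the area under the curve of APACHE-II and Marshall scores from randomization to day 7 will be calculated and compared between treatment groups". No baseline term is mentioned, although Descriptive statistics lists both scores among the variables recorded before randomisation.

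**The concern.** Patients were stratified on APACHE-II because it is taken to predict severity. Balancing the arms on a prognostic factor removes some chance variation from the treatment comparison. An unadjusted standard error does not credit that removal. The interval is then somewhat too wide and the test runs a little below its nominal 5%. The power given up could be recovered at no cost.

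The authors name covariates where they want them, in the timing model, and name none for the primary comparison. Both stratifiers therefore appear in an exploratory model that cannot estimate the effect of allocation, and neither appears in the analysis that decides the trial.

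Two lesser points follow the same line. The score AUCs begin at randomisation and so contain the pre-treatment value, yet no adjustment for it is stated. The APACHE-II subgroup analysis is announced without saying that the strata will be compared through an interaction.

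**Working it through.** **1. The plan's own figure.** Sample size calculation states that "an absolute reduction of 18% is expected (from 40 to 22" per cent), with 80% power, two-sided 5% and 1% loss. With the pooled-variance formula and mean risk 0.31:

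n per arm = [1.96·√(2·0.31·0.69) + 0.842·√(0.40·0.60 + 0.22·0.78)]² / 0.18² = 102.4, so 103.

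That is 206 in total, and 206/0.99 = 208.1, against 208 stated. At 104 per arm the same formula gives 80.6% power. The planned size is reproduced as an unadjusted two-proportion comparison and is sound.

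**2. Unadjusted precision.** SE(log RR) = √[(0.60/0.40 + 0.78/0.22)/104] = 0.220. The 95% interval around 0.55 is 0.36 to 0.85.

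**3. Gain from stratifying by APACHE-II, one case in full.** Assume 30% at ≥13 with twice the risk of the rest.

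- Control: 0.40/1.3 = 0.308 and 0.615. Within-stratum variance = 0.7·0.308·0.692 + 0.3·0.615·0.385 = 0.220, against 0.240 in total.
- Early EN: 0.169 and 0.338. Within-stratum variance 0.166, against 0.172 in total.
- Stratified SE(log RR) = √[(0.2201/0.16 + 0.1656/0.0484)/104] = 0.215, so the interval is 2.5% narrower.
- Power from 0.18/√(variance sum/104) − 1.96: 81.6% unadjusted, 84.0% stratified. This uses unpooled variance, hence 81.6% rather than the 80.6% of step 1.

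The same calculation with 20–40% of patients at ≥13:

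| Risk ratio, ≥13 vs <13 (assumed) | Interval narrower by | Power gained |
|---|---|---|
| 1 | 0 | 0 |
| 1.5 | 0.7–0.8% | 0.7–0.8 points |
| 2 | 2.2–2.5% | 2.2–2.4 points |
| 3 | 6–7% | 5.8–6.4 points |

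**4. Type I error.** If there is no effect and the arms are balanced within strata, the unadjusted statistic has standard deviation √(within/total variance). In the case above this is √(0.2201/0.24) = 0.958. The test then rejects when |Z| > 1.96/0.958 = 2.05, which has probability 4.1%.

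**5. Simulation.** 40,000 trials of 208, balanced within APACHE-II stratum, unadjusted test against CMH:

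| Share ≥13; control risks (assumed) | Type I error | Power at RR 0.55 |
|---|---|---|
| 25%; 33% / 61% | 4.5% vs 4.9% | 81.6% vs 82.5% |
| 30%; 30% / 63% | 4.1% vs 4.9% | 81.6% vs 83.2% |
| 30%; 25% / 75% | 2.9% vs 5.0% | 83.0% vs 86.8% |

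The gains are 0.9, 1.6 and 3.8 points, somewhat below the approximation in step 3.

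A smaller simulation (5,000 runs) placed blocks of an assumed size 2 or 4 within 20 hospitals by two APACHE-II strata. With 30% at ≥13 and a stratum risk ratio of 2 it gave an unadjusted type I error of 4.7%, and power of 80.7% unadjusted against 82.6% stratified. With added hospital variation (log-SD 0.3) the unadjusted type I error fell to 3.6%, and stratifying by APACHE-II alone brought it to 4.4%.

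**6. Hospital.** 20 hospitals × 2 strata = 40 cells, and 208/40 ≈ 5 patients per cell.

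**7. AUC.** Baseline adjustment multiplies the standard error by √(1 − ρ²): 0.95, 0.87 and 0.71 for assumed correlations of 0.3, 0.5 and 0.7.

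**8. Subgroups.** Take a true risk ratio of 0.55 in both strata (30% at ≥13; 30%/63%). If each stratum were tested separately, exactly one would reach P < 0.05 in about 50% of simulated trials.

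**The case against.** The strongest reply is that the article never calls the risk ratio unadjusted. It names no estimator, a Mantel-Haenszel ratio would satisfy its wording, and a full protocol or SAP that is not shown may settle the matter. It stands that the unadjusted reading is an inference. The inference is still the natural one: covariates are listed for the timing model and none for the primary comparison, and the sample size follows an unadjusted formula.

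It also stands that the loss is small and rests on assumed stratum risks. The 75%/25% split in particular has no basis in the article. Adjusting for APACHE-II alone also leaves the hospital stratifier unused, but with about five patients per cell that is a matter of judgement.

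A reader might infer more than the article supports:

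- *That the trial is underpowered.* Unadjusted power is 80.6% or more at the design effect by calculation, which meets the stated 80%.
- *That the primary result could be falsely positive.* Ignoring the strata makes the test conservative, so the error runs the other way.
- *That early deaths make an AUC look favourable.* This assumes summing over observed days only. The article states no rule for deaths, and the scores are additional analyses.
- *That the subgroups will be tested one by one.* The article does not say so and does not exclude an interaction test.

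**Conclusion.** The point holds as a modest loss of efficiency. The design stratifies on APACHE-II, and the primary comparison as written does not use it. With 25–30% of patients at ≥13 and about double the risk there, the unadjusted test runs at about 4.1–4.5% and gives up about 1–2 power points at a risk ratio of 0.55. A 75%/25% split would cost about 4 points, and a non-prognostic stratum nothing. All of these rest on assumed shares and risks.

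The treatment estimate is not biased, false positives are not inflated, and the sample size needs no change. Leaving baseline out of the AUC comparison likewise costs precision without biasing it. The subgroup point is a precaution against reading a difference between strata into two separate P values.

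**What to change.** **Primary.** State that the primary analysis is a Mantel-Haenszel risk ratio with 95% interval and a CMH test, stratified by APACHE-II <13/≥13 as used at randomisation. Show the unadjusted risk ratio alongside, and use the same stratified test at the interim analysis.

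**Hospital.** Use hospital in a sensitivity analysis only, with small sites pooled or a random hospital effect. Separate fixed effects over up to 40 cells would be too sparse.

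**Lower priority.** Compare the APACHE-II and Marshall AUCs by ANCOVA on the pre-randomisation score. Report the treatment-by-APACHE-II interaction on the primary endpoint with its interval, and base any statement about the subgroups on that.

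**Cost.** A few lines of analysis text. Both stratifiers and both baseline scores are recorded before randomisation, and no extra patients are needed. The article reports 142 patients already randomised, so the change should be dated and made by people who have not seen outcomes by arm. If the full protocol or SAP already specifies a stratified analysis, only the lower-priority items need checking.
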